#### Regression modeling (aim 2)

a) In keeping with target trial emulation methodology as described above, the index date for patients exposed to anticoagulation will be the date of the first anticoagulant prescription drug claim occurring after the diagnosis of AF. For potential controls, only patients with no exposure to anticoagulation throughout the study period would be eligible to avoid selecting controls who start an anticoagulant during the follow-up period. For controls, inclusion and exclusion criteria will be examined for each year after AF diagnosis, and the midpoint of one random year will be selected as the index date for each control patient.b) Similar to Aim 1, patients diagnosed with CRAO precedent to or concurrent to AF diagnosis will be excluded and these patients will be examined in an exploratory analysis.c) Our primary analysis will utilize propensity score overlap weighting methodology to approximate a randomized design where baseline hazard of CRAO of patients receiving anticoagulation vs. not receiving is comparable. We will incorporate the following variables to define the propensity score: age, time since first AF claim, sex, geography, race, Medicaid dual eligibility, vascular comorbidities and non-vascular comorbidities relevant to the likelihood that a patient will be treated with anticoagulation (to include all of the comorbidity variables included for Aim 1 propensity score, as well as history of gastrointestinal bleeding or peptic ulcer disease (using validated ICD-9-CM codes 531.x (gastric ulcer), 532.x (duodenal ulcer), and 578.x (gastrointestinal hemorrhage) and their ICD-10-CM counterparts K25.x, K26.x, and K92.2) and history of intracranial hemorrhage (any of ICD-10-CM I60, I61, S06.3, S06.4, S06.5, S06.6 and their ICD-9-CM counterparts 430.x, 431.x, 432.x)) [32–35].d) Our principal effect of interest is the hazard of CRAO among patients treated with any oral anticoagulant agent compared to those not treated. Given variable patient adherence to anticoagulation, we will take advantage of the strength of Part D data (which records pharmaceutical fills rather than prescriptions) and treat anticoagulation exposure as a time-varying covariate for patients exposed to anticoagulation.e) We will perform identical sensitivity analyses as described in Aim 1.f) Table shells for the results of Aim 2 are shown in Table 8.

**Table 8 pone.0296251.t008:** Results of cause-specific hazard regression modeling for Aim 2, hazard of outcome based on time-varying exposure to anticoagulation.

Outcome	Unadjusted Model	Adjusted Model†
CRAO (Overlap weighted)	HR (95% CI)	aHR (95% CI)
CRAO (primary dx)	HR (95% CI)	aHR (95% CI)
Any RAO	HR (95% CI)	aHR (95% CI)
CRAO (any dx position)	HR (95% CI)	aHR (95% CI)
Intracranial Hemorrhage	HR (95% CI)	aHR (95% CI)
Ischemic Stroke	HR (95% CI)	aHR (95% CI)
UTI	HR (95% CI)	aHR (95% CI)

^†^This column reflects the results of a model that incorporates overlap weighting using propensity scores re-estimated after our first stage matching procedure.

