### Design and setting

Retrospective, observational, population-level cohort study of patients with atrial fibrillation and matched controls using administrative claims data among a 5% sample of fee-for-service Medicare beneficiaries in the United States from 2000–2020. This data source allows us to follow unique patients longitudinally for the duration of their fee-for-service enrollment, regardless of state of residence.

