### Outcome

The outcome of interest is incident central retinal artery occlusion. Central retinal artery occlusion will be identified through ICD-9-CM 362.31, which we validated in a prior study [13] in the primary diagnosis position in any emergency department, inpatient, or outpatient claim. We will use the corresponding ICD-10-CM code H34.1x for claims occurring after September 31, 2015.

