**Charlson Comorbidity Variables**			
Myocardial Infarction	410.*, 412.*	I21.*, I22.*, I25.2*	Quan, 2005 [20]
Congestive Heart Failure	398.91, 402.01, 402.11, 402.91, 404.01, 404.03, 404.11, 404.13, 404.91, 404.93, 425.4, 425.5, 425.7, 425.8, 425.9, 428*	I09.81, I11.0*, I13.0*, I13.2*, I42.0*, I42.5*-I42.9*, I43.*, I50.*	Quan, 2005 [20]
Peripheral Vascular Disease	093.0*, 437.3*, 440.*, 441.*, 443.1*, 443.2*, 443.8*, 443.9*, 447.1*, 557.1*, 557.9*, V43.4*	A52.01*, E08.51, E08.52, E09.51, E09.52, E10.51, E10.52, E11.51, E11.52, E13.51, E13.52, I67.0*, I67.1*, I70.*, I71.*, I73.1*, I73.8*, I73.9*, I77.7*, I79.*, K55.1*, K55.8*, K55.9*, Z958.2*	Quan, 2005 [20]
Cerebrovascular Disease†††	430*, 431*, 432.*, 433.*, 434.*, 435.*, 436*, 437.*, 438.*	G45.0, G45.1, G45.2, G45.4, G45.8, G45.9, G46.*, I60.*-I63.*, I65.*-I66.*, I67.1*, I67.2*, I67.4*, I67.5*, I67.6*-I67.7*, I67.81, I67.82, I67.84, I67.89, I67.9*, I68.*-I69.*	Quan, 2005[20]
Dementia	290.*, 294.1*, 331.2*	F01.*, F02.*, F03.9*, G31.1*	Quan, 2005 [20]
Chronic Pulmonary Disease	416.8*, 416.9*, 490*, 491.*, 492.*, 493.*, 494.*, 495.*, 496*, 500*, 501*, 502*, 503*, 504*, 505*, 506.4*, 508.1*, 508.8*	I27.2*, I27.81, I27.89, I27.9*, J40.*-J44.*, J45.2*-J45.5*, J45.90, J45.99, J47.*, J60.*, J61.*-J67, J68.4*, J70.1*, J70.2*, J70.3*, J70.4*, J70.8*	Quan, 2005 [20]
Connective Tissue Disease	446.5*, 710.0*, 710.1*, 710.2*, 710.3*, 710.4*, 714.0*, 714.1*, 714.2*, 714.8*, 725*	M05.*, M06.*, M31.5*, M31.6*, M32.*-M34.*, M35.0*, M35.3*, M36.0*	Quan, 2005 [20]
Peptic Ulcer Disease	531.*, 532.*, 533.*, 534.*	K25.*-K28.*	Quan, 2005 [20]
Mild Liver Disease	070.22, 070.23, 070.32, 070.33, 070.44, 070.54, 070.6*, 070.9*, 570*, 571.*, 573.3*, 573.4*, 573.8*, 573.9*, V42.7*	B17.9*, B18.0*-B18.2*, B19.0*, B19.9*, K70.0, K70.1*, K70.2, K70.3*, K70.40, K70.9, K71.*, K72.00, K73.*, K74.0*, K74.1*-K74.6*, K75.2*-K75.4*, K75.8*, K75.9*, K76.0*-K76.5*, K76.89, K76.9*, K77.*, Z48.23, Z94.4*	Quan, 2005 [20]
Diabetes without complications	250.0*, 250.1*, 250.2*, 250.3*, 250.8*, 250.9*	E10.1*, E10.618, E10.62*, E10.63, E10.64, E10.65, E10.69, E10.8*, E10.9*, E11.0*, E11.1*, E11.618, E11.62-E11.65, E11.69, E11.8*, E11.9*, E13.00, E13.01, E13.10, E13.11, E13.618, E13.62-E13.65, E13.69, E13.8*, E13.9*	Quan, 2005 [20]
Diabetes with complication	250.4*, 250.5*, 250.6*, 250.7*	E10.2*-E10.5*, E10.610, E11.2*-E11.5*, E11.610, E13.2*-E13.5*, E13.610	Quan, 2005 [20]

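### In the Aim 2 propensity score, the gastrointestinal-bleeding covariate uses all of ICD-9-CM 578.x but only K92.2 in ICD-10-CM, so histories coded solely as hematemesis or melena drop out after the changeover

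*Protocol article*

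**What the plan says.** Item c of Regression modeling (aim 2) lists the propensity-score variables. They include "non-vascular comorbidities relevant to the likelihood that a patient will be treated with anticoagulation", and one of these is a history of gastrointestinal bleeding or peptic ulcer. The ICD-9-CM side is introduced as "using validated ICD-9-CM codes 531.x (gastric ulcer), 532.x (duodenal ulcer"). The sentence then completes the ICD-9-CM list and gives the ICD-10-CM side: "578.x (gastrointestinal hemorrhage) and their ICD-10-CM counterparts K25.x, K26.x, and K92.2".

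The remaining demographic and timing variables are "age, time since first AF claim, sex, geography, race, Medicaid dual eligibility". Neither calendar year nor coding era is listed.

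Design and setting describes a "5% sample of fee-for-service Medicare beneficiaries in the United States from 2000–2020", so both coding systems contribute. The changeover date appears only for the outcome, in the Outcome section: "corresponding ICD-10-CM code H34.1x for claims occurring after September 31, 2015". That date does not exist; I read it as ICD-10-CM from 1 October 2015. Adjustment covariates sets a twelve-month look-back for comorbidities.

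The Charlson peptic ulcer row of Table 2 uses "531.*, 532.*, 533.*, 534" in ICD-9-CM and K25 to K28 in ICD-10-CM.

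**The concern.** A covariate built from diagnosis codes should mean the same thing on both sides of a coding change. Here the hemorrhage part does not: a whole ICD-9-CM category is paired with a single ICD-10-CM code, although the text presents the two lists as equivalent.

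The variable is in the score because it bears on who receives anticoagulation. Overlap weighting balances the flag as recorded. After the changeover, patients coded only with hematemesis or melena are balanced as if they had no bleeding history, and a standardized difference near zero would not show it. The Table 4 shell has no row for this covariate, so a reader of the results would not see a change in its prevalence either.

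The CRAO hazard ratio for Aim 2 is at stake. So, possibly, is the check on intracranial hemorrhage in Table 8, because Limitations counts reproducing the known excess of that outcome as support for the CRAO result.

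**Working it through.** **1. The two lists side by side.** No figure in the protocol needs reproducing; this is a code-list comparison.

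| Part of the covariate | ICD-9-CM | ICD-10-CM | Equivalent? |
|---|---|---|---|
| Gastric ulcer | 531.x | K25.x | yes |
| Duodenal ulcer | 532.x | K26.x | yes |
| Hemorrhage | 578.x (whole category) | K92.2 (one code) | no |

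In the public code sets, 578 covers hematemesis, blood in stool or melena, and unspecified hemorrhage. K92.2 corresponds to the unspecified code; K92.0 and K92.1 correspond to the other two. No row of Table 2 lists K92.0 or K92.1, and the Charlson peptic ulcer row covers ulcers only.

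**2. Who is affected.** Only a patient whose look-back falls in the ICD-10 era and holds K92.0 or K92.1 but no K92.2, K25.x or K26.x. I assume that the twelve-month look-back also governs this Aim 2 covariate, since no other is given.

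**3. Share of index years.** With the twelve-month look-back, index dates from about October 2016 rest on ICD-10-CM alone. Aim 2 asks for twelve months of enrollment after index, or until death, so almost no 2020 index date qualifies. The fully affected window is October 2016 to December 2019, which is 3.25 years.

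- Index years 2001 to 2019: 3.25/19 = 17%.
- Index years 2006 to 2019, if Part D data start in 2006 (assumption): 3.25/14 = 23%.

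Both assume even accrual. October 2015 to September 2016 is partly affected. Counting it in full gives an upper bound of 4.25/14 = 30%.

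**4. Size within the ICD-10 era.** Every input is assumed. With bleeding prevalence p1 in treated and p0 in untreated patients, outcome ratio RR and missed fraction f:

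bias factor = [1 + p1(RR − 1)f] / [1 + p0(RR − 1)f]

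- p1 = 3%, p0 = 8%, RR = 1.3, f = 0.2: 1.0018/1.0048 = 0.997.
- p1 = 4%, p0 = 10%, RR = 1.5, f = 0.5: 1.010/1.025 = 0.985.
- As the second, with p1 = 3%: 1.0075/1.025 = 0.983.

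**5. A harsher set.** Let u be the share of flagged patients who qualify only through 578.x, and s the share of those who would carry K92.2. The ICD-10 flag then captures r = 1 − u(1 − s) of what the ICD-9 flag would. With u = 0.3 and s = 0.9, r = 0.97; with u = 0.9 and s = 0.3, r = 0.37. Take bleeding prevalence of 5% in treated and 15% in untreated patients. The missed bleeders among the unflagged are q = p(1 − r)/(1 − pr), and the residual confounding ratio is [1 + q1(RR − 1)]/[1 + q0(RR − 1)].

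- r = 0.97, RR = 1.5: 0.998.
- r = 0.37, RR = 1.5: 0.968.
- r = 0.37, RR = 2: q1 = 0.032, q0 = 0.100, ratio 1.032/1.100 = 0.938.

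**6. Pooled over all index years,** if events are spread evenly over them: 0.3% × 0.17 = 0.05% up to 1.5% × 0.23 = 0.35% on the moderate inputs, and 6.2% × 0.23 = 1.4% on the harshest.

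**The case against.** The strongest reply is that this is immaterial. CRAO is rare. With 1,000 events split equally (an assumption), the standard error of the log hazard ratio is √(1/500 + 1/500) = 0.063, and the 95% limits lie about 13% either side of the estimate. A pooled shift below 1% could not change a conclusion. The formulas also treat missed bleeders as wholly unadjusted, although correlated covariates such as ulcer, liver and renal disease stay in the score. Limitations acknowledges residual confounding, and control outcomes are planned. All of this stands. It limits severity but does not make the lists equivalent.

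A second reply is that the protocol does not spell out the contents of 578, and its cited sources, which I have not seen, may use K92.2 alone. The mismatch is nevertheless visible in the sentence itself, the code sets are public, and the claim of validation is attached to the ICD-9-CM codes.

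Stronger readings are tempting but not supported:

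- A reader might infer that a main reason for withholding anticoagulation goes unrecorded. The protocol says only that these comorbidities bear on the likelihood of treatment, and ulcer codes and K92.2 are still captured.
- A reader might take the affected share as 5.25/21 = 25% or 5.25/15 = 35%. Those are calendar shares that ignore the look-back and follow-up rules.
- A reader might conclude that the bias favors anticoagulation. That needs a bleeding-CRAO ratio above 1, which nothing in the document establishes.
- A reader might expect a larger effect on intracranial hemorrhage. No input supports a figure, and prior intracranial hemorrhage is a separate variable in the score.

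**Conclusion.** The point holds as a minor code-list error. The ICD-10-CM list is narrower than the ICD-9-CM list it is said to match, and it under-records bleeding history for patients coded only with hematemesis or melena. That under-recording is certain in direction; its frequency is unknown.

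About 17% to 23% of index years are fully affected, under the accrual and Part D assumptions above. The likely effect on the CRAO hazard ratio is small: about 0.3% to 1.5% within the ICD-10 era on moderate assumptions, well under 1% pooled. About 6% within the era is reached only if nearly all flagged patients qualify through 578.x alone, few of them carry K92.2, and bleeding doubles CRAO risk. The sign depends on the assumed bleeding-CRAO association. The case for correction is that the text should be true to itself and the edit is trivial, not that the Aim 2 result is in danger.

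**What to change.** In item c of Regression modeling (aim 2), give the ICD-10-CM codes as K25.x, K26.x and K92.0 to K92.2, so that they match 531.x, 532.x and 578.x. Then plot the monthly prevalence of the flag across October 2015, preferably by treatment group, to confirm that there is no step. If one remains, index year could be added to the propensity score.

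The cost is two codes in a look-up list and one plot. No new data are needed, and I see no analytic downside.

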### Limitations

The principal limitation of this study is its observational, retrospective nature. Unfortunately, the incidence of CRAO is low, and evaluating the effect of anticoagulation on primary or recurrent CRAO risk is likely to be infeasible given the massive study sizes that would be required to detect an effect. While our target trial emulation methodology, including careful selection of index date and control patients and our use of overlap weighting methodology, can help to answer this question to its best extent using real-world data, the potential for residual confounding is still present in any observational data source. Additional limitations include the use of Medicare data, which has several intrinsic limitations, including having a limited number of beneficiaries under the age of 65, lacking access to clinical data not captured in structured claims, and limited ascertainment of key information on demographic identity, including gender identity and race/ethnicity. Another limitation in any non-controlled study of anticoagulation is the fact that the antithrombotic effect of anticoagulation varies according to patient adherence, especially for patients taking Warfarin. The use of Medicare Part D data has one major advantage in that it captures medication fills, not medication prescriptions, therefore giving a better surrogate of patient adherence, although some patients may not take medications that they nonetheless fill, recognizing that generalizability may be limited to Part D enrollees. Treating exposure to anticoagulation as a time-varying covariate will also help to capture more precisely the effect that therapeutic anticoagulation has on CRAO risk. Furthermore, our use of both positive and negative control endpoints in this analysis should help to interpret our eventual findings: existing evidence from randomized controlled trials has shown that use of anticoagulation is highly effective in preventing embolic stroke due to atrial fibrillation, and is associated with an increased risk of intracranial hemorrhage; if we replicate these results in our study design, it gives increased confidence that our results concerning CRAO may be valid. Finally, some patients with contraindication to oral anticoagulation may receive alternative management strategies that can decrease their ischemic stroke risk, such as receipt of a left atrial appendage occlusion device. We address this limitation through a sensitivity analysis excluding any patient who receives a LAAO during the study follow-up period or with a diagnostic code indicating the placement of an LAAO in the comorbidity ascertainment window.

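### Aim 2's history-of-intracranial-hemorrhage covariate uses ICD-9 and ICD-10 code lists that do not cover the same conditions

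*Protocol article*

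**What the plan says.** Regression modeling (aim 2), item c), sets out the propensity score for anticoagulated versus untreated patients: "We will incorporate the following variables to define the propensity score: age, time since first AF claim, sex, geography, race, Medicaid dual eligibility", followed by comorbidities. These include all the Aim 1 comorbidity variables plus bleeding histories. The intracranial hemorrhage history is coded as "any of ICD-10-CM I60, I61, S06.3, S06.4, S06.5, S06.6 and their ICD-9-CM counterparts 430.x, 431.x, 432.x".

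Table 2 has a cerebrovascular disease group that covers part of the same ground. Its ICD-9 column reads "430*, 431*, 432.*, 433.*, 434.*, 435.*, 436*, 437.*, 438". Its ICD-10 column includes "I60.*-I63.*, I65.*-I66" and no S06 code.

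Design and setting gives a study period of 2000 to 2020. The Outcome section places the change of coding system in autumn 2015: "We will use the corresponding ICD-10-CM code H34.1x for claims occurring after September 31, 2015". Adjustment covariates sets a twelve-month look-back from the index date.

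Separately, the Table 8 shell has an outcome row "Intracranial Hemorrhage" without codes. Limitations treats that outcome as a check on the design, noting that anticoagulation "is associated with an increased risk of intracranial hemorrhage; if we replicate these results in our study design", which would add confidence in the CRAO result.

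**The concern.** The article presents the two lists as equivalents, so an analyst would program them as one variable. If they are not equivalent, a patient with a given bleed is flagged or not flagged according to the coding system in force during the look-back.

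A past intracranial bleed is in the score because it bears on whether a patient is anticoagulated. Overlap weighting balances the covariate as it was measured. A standardized difference near zero would therefore say nothing about whether the true bleeding history is balanced when the measurement changes partway through the study.

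**Working it through.** There is no stated figure to reproduce. The check compares the lists as sets and then asks whether a size can be derived. That S06 belongs to the injury chapter, and that 432 corresponds to I62, rests on the standard structure of the classification; the article does not spell out what the codes mean.

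**Step 1. Match the lists, then see what Table 2 also captures.**

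| Bleed type | Hemorrhage covariate, ICD-9 | Hemorrhage covariate, ICD-10 | Table 2 cerebrovascular group, ICD-9 | Table 2 cerebrovascular group, ICD-10 |
|---|---|---|---|---|
| 430 / I60 | yes | yes | yes | yes |
| 431 / I61 | yes | yes | yes | yes |
| 432 / I62 | yes | **no** | yes | yes |
| Injury codes / S06.3-S06.6 | **no** | **yes** | no | no |

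Unmatched: 1 of 3 ICD-9 categories (432) and 4 of 6 ICD-10 entries (S06.3, S06.4, S06.5, S06.6).

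**Step 2. What the covariate means in each era.** Before the switch it is non-traumatic bleeding of all three categories. After it, traumatic bleeding comes in and the third non-traumatic category goes out. For a patient indexed in the year after the switch, the twelve-month look-back straddles both systems and the flag is a mixture.

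**Step 3. Both eras carry weight.** Months under ICD-9, January 2000 to September 2015: 15 × 12 + 9 = 189. Months under ICD-10, October 2015 to December 2020: 5 × 12 + 3 = 63. Total 252, so 189/252 = 75% and 63/252 = 25%. These are calendar shares of the study period. The Aim 2 shares will differ, because that cohort needs Part D enrollment.

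**Step 4. Could the error differ between groups?** Index year is not among the listed propensity variables; elapsed time since the first AF claim is not calendar time. Exposed patients are indexed at their first anticoagulant claim, untreated patients at the midpoint of a randomly chosen eligible year. The two index-year distributions could therefore differ, and the mismatch with them. The article reports neither distribution, so this remains a possibility.

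**Step 5. Can a size be given?** Among all bleeds covered by either list, let b be the share in the third non-traumatic category and c the traumatic share. The ICD-9 list captures 1 − c and the ICD-10 list 1 − b, so the after-to-before ratio is (1 − b)/(1 − c). The article gives neither share. Under assumed ranges of b = 0.10 to 0.30 and c = 0.20 to 0.50:

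- b = 0.30, c = 0.20: 0.70/0.80 = 0.88
- b = 0.15, c = 0.35: 0.85/0.65 = 1.31
- b = 0.10, c = 0.50: 0.90/0.50 = 1.80

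Even the direction of the change in flagged patients is not determined. What is determined is that the flag stands for a different mix of conditions.

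**The case against.** **The covariate is partly backed up.** The Aim 1 comorbidities also enter the Aim 2 score, so 432 and I62 bleeds are still counted through the cerebrovascular group. This stands, and it softens the I62 omission. It does not remove it: that group pools bleeding with stroke/TIA and carotid stenosis, so it cannot stand in for a bleeding history. It does nothing for traumatic bleeds, which before the switch are in neither list.

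**Table 2 is not a crosswalk.** It sets one pooled ICD-9 group beside one pooled ICD-10 list and does not map code to code. This is correct. Table 2 shows that the I62 omission is at odds with the article's own grouping, and no more. The unmatched S06 codes are visible from the hemorrhage lists alone, given the chapter assumption above.

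**Stronger readings that a reader might infer, and why they are not supported:**

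- *That this list defines the Table 8 hemorrhage outcome.* It is the only hemorrhage list in the article, but it is written for the history covariate and nothing links it to Table 8. The outcome's codes may stand in a fuller plan, so their absence from a condensed article is not a fault. Nor would a changing mix of bleed types by itself defeat the directional check in Limitations.
- *That the hemorrhage hazard ratio loses precision.* If 20-40% of bleeds lost their code, the standard error would grow by 1/√(1 − s), that is 1.12 to 1.29. That share has no source in the article, and the sum ignores the S06 cases that are added. On the Step 5 extremes the net factor is 1/√0.875 = 1.07 to 1/√1.80 = 0.75.
- *That differential bias is established.* It would need different index-year distributions and a material prevalence of the unmatched codes within the look-back. The article shows neither.
- *That 578.x paired with K92.2 in the same sentence is a second mismatch.* The article offers no other pairing to set against it, so no error is demonstrated.

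**Conclusion.** The point holds for the Aim 2 covariate. Followed as written, the lists described as counterparts capture different conditions before and after the 2015 switch. This is a minor but plain error in a definition that the article itself fixes.

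Its effect on the Aim 2 hazard ratio cannot be sized from the documents. It depends on the prevalence of the unmatched codes in the look-back, the case mix, and the index-year distribution in each group, none of which is given. Partial cover from the cerebrovascular group reduces the likely harm. The CRAO definition, Aim 1 and the sample size are not touched. The conclusion assumes the standard chapter structure of the two coding systems.

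**What to change.** Use one clinical definition in both coding eras and state which was chosen:

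- **Non-traumatic only:** ICD-9-CM 430-432 with ICD-10-CM I60-I62, dropping S06.3-S06.6; or
- **All intracranial hemorrhage:** add I62 to the ICD-10 list and the traumatic intracranial hemorrhage categories to the ICD-9 list.

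If the Table 8 hemorrhage outcome is built from the same list, apply the harmonised version there as well, since Limitations relies on that outcome as a check.

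The cost is a correction to a code list. No new data, sample size or model is needed.

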### Exposure

The primary exposure of interest is prevalent atrial fibrillation/atrial flutter. Atrial fibrillation/atrial flutter will be defined through ICD-9-CM 427.13 or ICD-10-CM code I48 in 2 outpatient claims or one inpatient claim within 365 days [16–18]. Episodes of atrial fibrillation within 1 month of inpatient surgery will be excluded to avoid including patients with isolated post-operative atrial fibrillation [19].

The secondary exposure of interest (among patients with atrial fibrillation) is exposure to anticoagulation. For our secondary analysis (Objective 2), we will utilize Medicare Part D prescription drug claims to identify patients taking a direct acting oral anticoagulant (DOAC) or warfarin.

A list of search terms to identify anticoagulant drugs will be utilized as per Table 1, below:

**Table 1 pone.0296251.t001:** Drug lookup queries for anticoagulant exposure.

Drug Name	
Warfarin	Part D claim for generic drug name like ‘%WARFARIN%’, summarized per month (90-day fills will be imputed to monthly indicators)
Apixaban	Part D claim for generic drug name like ‘%APIXABAN%’, summarized per month (90-day fills will be imputed to monthly indicators)
Dabigatran	Part D claim for generic drug name like ‘%DABIGATRAN%’, summarized per month (90-day fills will be imputed to monthly indicators)
Edoxaban	Part D claim for generic drug name like ‘%EDOXABAN%’, summarized per month (90-day fills will be imputed to monthly indicators)
Rivaroxaban	Part D claim for generic drug name like ‘%RIVAROXABAN%’, summarized per month (90-day fills will be imputed to monthly indicators)

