### Adjustment covariates

We will utilize the following pre-specified covariates for risk adjustment: age, biological sex, race/ethnicity, and cardiovascular comorbidities and medical risk factors, including the medical comorbidities included in the Charlson Comorbidity Index (except for cardiac arrhythmias, which subsumes our primary exposure of interest), and additionally including hypertension, hyperlipidemia, valvular heart disease, and smoking status, using validated ICD-9-CM and ICD-10-CM algorithms [20–23]. Carotid stenosis and Stroke/TIA are contained in the cerebrovascular disease group of the Charlson Comorbidity Index. S1 and S2 Figs show the directional acyclic graphs representing our understanding of possible confounding variables.

We will ascertain comorbidities using a twelve-month look-back period from the patient’s index date (July 1 of initial year of inclusion in cohort for controls) using established claims-based algorithms. These are outlined in Table 2, below.

**Table 2 pone.0296251.t002:** List of international classification of diseases codes used for comorbidity adjustment.

Comorbidity	ICD-9 Code	ICD-10 Code	Citation
Hypertension	401.*, 402.*, 403.*, 404.*, 405.*, 437.2*	I10.*-I13.*, I15.0, I15.2, I15.8, I15.9, I16.*, I67.4*	Birman-Deych, 2005 [21]
Hyperlipidemia†	272.x	E78.x	Oake, 2017 [22]
Tobacco Use††	305.1, 649.0x, 989.84, V15.82; CPT codes 99406, 99407, G0436, G0437, G9016, S9453, S4995, G9276, G9458, 1034 F 4004 F 4001 F	F17.x, T65.2xx, Z87.891, CPT codes 99406, 99407, G0436, G0437, G9016, S9453, S4995, G9276, G9458, 1034 F 4004 F 4001 F	Desai, 2016 [23]
Valvular Heart Disease	394.*, 395.*, 396.*, 397.*, 398.9*, V42.2*, V43.3*, 424.*	I05.*-I08.*, I09.1*, I09.81, I09.89, I09.9*, I34.*-I39.*, Z95.2*, Z95.3*, Z95.4*	Birman-Deych, 2005 [21]

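### Aim 2 reports a time-varying on/off hazard ratio, but its weights balance only initiators and never-users at index, and nothing handles post-index reasons for stopping

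*Protocol article*

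**What the plan says.** All references are to the protocol article.

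- **Groups.** Under Regression modeling (aim 2), item a, an exposed patient's index date is "the date of the first anticoagulant prescription drug claim occurring after the diagnosis of AF". Controls are patients with no anticoagulant exposure at any time in the study period. Membership is thus initiator versus never-user, set at index.
- **Weights.** Item c uses propensity score overlap weighting to "approximate a randomized design where baseline hazard of CRAO of patients receiving anticoagulation vs. not receiving is comparable". The listed predictors begin with "age, time since first AF claim, sex, geography, race, Medicaid dual eligibility" and continue with comorbidity and bleeding history. The section on adjustment covariates sets the timing: "We will ascertain comorbidities using a twelve-month look-back period from" the index date. No predictor is measured after index.
- **Effect.** Item d states: "Our principal effect of interest is the hazard of CRAO among patients treated with any oral anticoagulant agent compared to those not treated". Because adherence varies, it then says that, using Part D fills, the analysis will "treat anticoagulation exposure as a time-varying covariate for patients exposed to anticoagulation".
- **Reporting.** The title of Table 8 describes its results as the "hazard of outcome based on time-varying exposure to anticoagulation". The note to its adjusted column mentions one set of overlap weights and nothing time-updated.
- **Sensitivity analyses.** Item e carries over those of Aim 1, which concern outcome coding and the exclusion of patients with left atrial appendage occlusion.

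**The concern.** The weights and the reported hazard ratio answer different questions. The weights make two groups comparable on measured covariates on the day follow-up starts. The hazard ratio compares months on drug with months off drug. Unexposed time is therefore a mixture of never-users and initiators who have stopped, and the stoppers enter with weights derived from their status as initiators.

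Stopping happens after index and may depend on events after index, such as a bleed, declining kidney function or growing frailty. If those events also relate to the risk of central retinal artery occlusion (CRAO), on-drug and off-drug time differ in risk for reasons other than the drug, however well the groups were balanced at index. A drug with no effect could then appear protective or harmful in an analysis the article presents as quasi-randomized. This concerns Aim 2's principal effect in the only form its results table reports.

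**Working it through.** The article gives no sample size, event count or discontinuation figure for Aim 2, so there is no figure of its own to reproduce. The inputs below are assumptions, chosen to show a range.

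**Inputs (assumed).** True hazard ratio 1. Equal average risk, set to 1, in weighted initiators and weighted never-users. Equal total weight and follow-up in the two groups. A share of 0.3 of initiators stops halfway through follow-up and does not restart. Stoppers have r times the average initiator risk. The outcome model has no covariates.

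**Formulas.**
- Persisters' risk: p = (1 − 0.3r)/0.7, which keeps the initiators' average at 1.
- On-drug time: 0.7 + 0.15 = 0.85. On-drug hazard = (0.7p + 0.15r)/0.85.
- Off-drug time: 1 + 0.15 = 1.15. Off-drug hazard = (1 + 0.15r)/1.15.

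| r | p | stoppers vs persisters (r/p) | on | off | ratio |
|---|---|---|---|---|---|
| 0.7 | 1.129 | 0.62 | 0.895/0.85 = 1.053 | 1.105/1.15 = 0.961 | 1.10 |
| 1.0 | 1.000 | 1.00 | 0.850/0.85 = 1.000 | 1.150/1.15 = 1.000 | 1.00 |
| 1.3 | 0.871 | 1.49 | 0.805/0.85 = 0.947 | 1.195/1.15 = 1.039 | 0.91 |
| 1.5 | 0.786 | 1.91 | 0.775/0.85 = 0.912 | 1.225/1.15 = 1.065 | 0.86 |
| 2.0 | 0.571 | 3.50 | 0.700/0.85 = 0.824 | 1.300/1.15 = 1.130 | 0.73 |

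The index-fixed ratio is 1.00 in every row, but only because equal group risk was assumed.

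**Check with comparison within time.** A Cox model compares patients at the same time since index, whereas the table pools person-time. Splitting follow-up into two halves and combining them by Mantel-Haenszel gives a numerator of 0.25 + 0.35p × 0.65 and a denominator of 0.25 + (0.5 + 0.15r) × 0.35. The ratios are 0.507/0.462 = 1.10 (r = 0.7), 0.448/0.493 = 0.91 (1.3), 0.429/0.504 = 0.85 (1.5) and 0.380/0.530 = 0.72 (2.0). Pooling does not drive the result.

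**Check by simulation.** The set-up was 1.5 million patients, 36 months, a true hazard ratio of 1, overlap weights from the true propensity score, and month-stratified rate ratios. The baseline event hazard was 0.001 per month, far above that of CRAO, to give stable ratios. A factor arising after index raised both the event hazard and the chance of stopping, and patients with it did not restart.

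| Effect of the factor on monthly stopping | Hazard multiplied by 1.5 | by 2 | by 3 |
|---|---|---|---|
| Threefold | 0.93 | 0.89 | 0.84 |
| Sixfold | 0.92 | 0.85 | 0.76 |

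Across these runs the initiator versus never-user ratio stayed between 0.99 and 1.01. The factor was present in about 12% of on-drug time against 46% of initiators' off-drug time (threefold), and about 8% against 53% (sixfold). When stopping and restarting did not depend on the factor, the time-varying ratio was 1.005.

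**The case against.** **The randomized-design sentence concerns baseline hazard only, and Limitations admits residual confounding.** Both are true. Yet the baseline contrast that sentence supports is not the one Table 8 reports. Limitations presents the time-varying coding only as a gain and does not mention selective stopping.

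**Control outcomes would expose the problem.** Table 8 runs urinary tract infection, ischemic stroke and intracranial hemorrhage through the same model. If stoppers are generally sicker, the infection hazard ratio should move from 1. That is a useful warning, but it corrects nothing and may miss a mechanism specific to vascular risk. A protective stroke result could come from the drug, from selective stopping, or from both.

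**The outcome model may adjust for baseline covariates.** Aim 1 does so, and if Aim 2 follows suit, measured baseline predictors of stopping are partly handled. The Aim 2 text does not say this explicitly. Post-index and unmeasured causes of stopping remain in either case. The illustration allows for no such adjustment.

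**On-treatment effect is a legitimate target.** This stands. The authors chose it because adherence varies, and replacing it as primary would be partly a matter of preference.

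**Stronger readings.** Three further inferences are tempting, and the document supports none of them:
- That the bias must favor anticoagulation. With r below 1 it goes the other way, and nothing in the article indicates who stops.
- That the index-fixed hazard ratio would be unbiased. Controls are chosen for never using an anticoagulant later, and that contrast inherits this selection.
- That a fill made after an event would mark the event's month as exposed, because Table 1 says fills are "summarized per month (90-day fills will be imputed to monthly indicators". The article does not state how fills and events within a month are ordered, and an article commonly leaves that to programming detail.

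**Conclusion.** The mismatch is real and follows from choices the article itself fixes: predictors measured at or before index, one set of weights, and time-varying exposure as the only reported form. Baseline balance on measured covariates holds for initiators versus never-users. It does not extend to on-drug versus off-drug time unless stopping and restarting are unrelated to CRAO risk given what is adjusted for, an assumption the article neither states nor defends.

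Confidence is high on this structural point and low on its size. The illustrated range of 0.73 to 1.10 under a true hazard ratio of 1 rests entirely on assumed inputs, and its lower end needs stoppers to carry 3.5 times the persisters' risk. If fill gaps are unrelated to risk, the bias is negligible. The point should be addressed before analysis. It does not make Aim 2 unworkable.

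**What to change.** Amend Regression modeling (aim 2), items c and d, and Table 8:

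1. Keep the time-varying hazard ratio and label it the on-treatment estimate. Add time-updated inverse-probability weights for discontinuation and restarting, using claims covariates updated during follow-up.
2. Report beside it the overlap-weighted hazard ratio with exposure fixed at index (initiator versus non-user).
3. Limit the randomized-design wording to that baseline contrast, and state the assumption about stopping that the on-treatment estimate needs.

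The cost is one or two extra weighted models and revised wording, with no new data. Time-updated weights will widen the intervals somewhat. They also address only those reasons for stopping that claims record. The index-fixed hazard ratio is diluted by discontinuation and remains affected by choosing controls on future non-use, and the text should say so.
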